#### Prevalence Study

The specific objectives of this study include (1) evaluating the overall prevalence rate of workplace cyberbullying and its related psychological impacts (depression, anxiety, and stress) on TCM practitioner; (2) understanding the measures associated with various forms of workplace cyberbullying on age, gender, and frequency; and (3) understanding the measure associated with workplace cyberbullying on perpetrators responsible for workplace cyberbullying. The current research will be a survey-based online cross-sectional prevalence study. TCM practitioners are considered a hard-to-reach population; thus, we will conduct a nonprobability snowball sample of 1023 adults (3% precision, 95% confidence level) according to the number of TCM practitioners, which was approximately 15,000 in 2011 [16]. The Hamilton Depression Scale (HAM-D) [17], the Hamilton Anxiety Scale (HAM-A) [18], and the clinical anger scale [19] will be used to assess the psychological impact on TCM practitioners. The Cyberbullying Questionnaire (CBQ) and a short version of a cyberbullying behavior questionnaire (CBQ-S), adapted from Jönsson et al [20], will be used to identify the prevalence among TCM practitioners; these selected questionnaires were already validated in Sweden and the US adult population [20]. The prevalence will also investigate the association with moderating variables (age and gender). Perpetrators of cyberbullying will also be assessed in the specific identification of the prevalence of workplace cyberbullying using the CBQ and CBQ-S questionnaires. The sampling method to understand perpetrator effects in the prevalence will similarly be addressed. The survey will also include a socioeconomic assessment, including education, income, home characteristics, and commodities. The survey will be conducted online due to the current pandemic situation caused by COVID-19, following the CHERRIES guidelines given by Gunther Eysenbach [21].

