#### Exploratory Study

The purpose of the exploratory study is to understand the moderating and mediating factors of workplace cyberbullying by using the ERM on TCM practitioners [15]. The specific questions of this study include the following: (1) What are the relationships between emotions, workplace stressors, cyberbullying perpetration, cyberbullying victimization, and control appraisal, reappraisal, and suppression? (2) What effects do demographic factors have on emotions, workplace stressors, cyberbullying perpetration, cyberbullying victimization, and control appraisal, reappraisal, and suppression? The survey will be conducted using a convenience method, with a sample size of 384 (5% precision, 95% confidence level). A structural equation model will be developed, and each construct will be discussed. A snowball sampling method will be used to approach the target population. There will be a lucky draw at the end of the exploratory study on the participants; the 10 winners of the draw will receive an electronic power bank.

This procedure was selected due to a hard-to-reach study population and a study undertaken during the COVID-19 pandemic.

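### The exploratory study's 5% precision at n = 384 is a random-sample margin for one proportion and does not apply to a structural equation model fitted to a nonprobability sample

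*Protocol article*

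**What the plan says.** All of the following comes from the Exploratory Study section (Methods, Phase 1) of the protocol article.

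- **Size and its basis:** "The survey will be conducted using a convenience method, with a sample size of 384 (5% precision, 95% confidence level"). No other basis is given: no proportion, path size, power or design effect.
- **Aim:** "The purpose of the exploratory study is to understand the moderating and mediating factors of workplace cyberbullying by using the ERM on TCM practitioners".
- **First question:** "What are the relationships between emotions, workplace stressors, cyberbullying perpetration, cyberbullying victimization, and control appraisal, reappraisal, and suppression"? The second question asks how demographic factors affect the same constructs.
- **Analysis:** "A structural equation model will be developed, and each construct will be discussed".
- **Sampling:** "The survey will be conducted using a convenience method", and shortly afterwards, "A snowball sampling method will be used to approach the target population".

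Estimating prevalence belongs to a different study. The Prevalence Study section has its own sample of 1023 and its own 3% precision.

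**The concern.** A precision statement has meaning only for a named quantity under a named sampling scheme. Here the 5% is five percentage points on a proportion under simple random sampling. The exploratory study has neither element: its targets are path coefficients, indirect effects and interactions, and its participants arrive by convenience or referral.

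The third research question (moderating and mediating factors) depends largely on this survey, and Phase 2 is to start only after the prevalence and exploratory work. A reader who sees a 5% precision beside a structural equation model may credit its estimates with an accuracy that was never calculated for them. Referral sampling adds two problems that the formula ignores. People in the same referral chain tend to resemble one another, which widens the true uncertainty. Those reached may also differ from those not reached, which no margin of sampling error captures.

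**Working it through.** **Inputs from the protocol article:** n = 384, margin 0.05, confidence 95% (z = 1.96), a structural equation model, convenience or snowball sampling.

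**Assumed, because not stated:** p = 0.5 (chosen because it reproduces 384); correlations from 0 to 0.5; a design effect of 2 as an illustration.

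**1. Reproduce the stated figure.** The one-proportion formula is n = z² p(1 − p) / d².

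1.96² × 0.25 / 0.05² = 384.1

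In reverse, 1.96 × √(0.25 / 384) = 0.0500. The match is exact, so the source of the number is not in doubt and the arithmetic is right for that formula.

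**2. Compare with what is estimated.** The formula's target is one proportion. The section's targets are relationships among seven named constructs, mediating and moderating effects, and demographic effects. None is a proportion.

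**3. Precision for a quantity of the right kind.** For a correlation, the Fisher-z 95% interval is tanh(atanh(r) ± 1.96 / √(n − 3)). With n = 384, 1.96 / √381 = 0.1004. Half of the resulting interval width is:

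| True r | Half-width, independent sampling |
|---|---|
| 0 | ±0.100 |
| 0.2 | ±0.096 |
| 0.3 | ±0.091 |
| 0.5 | ±0.075 |

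**4. A rough proxy for a path with other predictors.** Take SE = √[(1 − R²) / ((1 − R²ₓ)(n − k − 1))] with k = 6, so n − k − 1 = 377. Here R² is the variance explained in the outcome and R²ₓ that in the predictor by the other predictors, each assumed to lie between 0 and 0.5.

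- R² = 0.5, R²ₓ = 0: 1.96 × √(0.5 / 377) = ±0.071
- R² = 0, R²ₓ = 0.5: 1.96 × √(1 / (0.5 × 377)) = ±0.143

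**5. Effect of referral clustering.** An assumed design effect of 2 gives an effective n of 384 / 2 = 192.

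- Correlation near zero: 1.96 / √189 = 0.143, or about ±0.14
- Correlation of 0.3: ±0.129
- Even for a proportion: 1.96 × √(0.25 / 192) = 0.071, so ±5 points becomes about ±7.1

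**6. Is 384 too small?** For a simple correlation test under random sampling, power at a true r of 0.15 is Φ(atanh(0.15) × √381 − 1.96) = 84%. At r = 0.20 it is 98%.

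**The case against.** The best defence is that this is a Phase 1 exploratory survey with no power claim. The standard errors reported in the end will come from the fitted model, not from the sample-size clause, and 384 is a workable size. All of that stands. It limits the consequence, but it does not make the stated precision true of this study.

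Convenience and snowball can also be read together, as a convenience survey whose participants are reached by referral; both are nonprobability methods. That reading is fair, so the wording is something to reconcile rather than a serious contradiction. How standard errors and indirect effects are handled may properly sit in an analysis plan that is not shown, and its absence here is not part of the point. Nor does all work on moderators rest on the 384, since the Prevalence Study section also looks at age and gender.

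A reader might go further in four ways that the documents do not support:

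- **That the study is half as precise as claimed.** Five percentage points on a proportion and 0.05 on a correlation are different scales. The figure does not transfer; it is not wrong by a factor of two.
- **That ±0.10 is the best achievable.** Stronger relationships are estimated more tightly, for example ±0.075 at r = 0.5.
- **That 384 conflicts with the Prevalence Study's use of a population size** ("according to the number of TCM practitioners, which was approximately 15,000 in 2011"). A finite-population correction at 15,000 would give about 375 here. But the same correction for 3% precision gives 1067 / (1 + 1066 / 15,000) = 996, not that section's 1023, so no common method is established from which 384 departs.
- **That paths below roughly 0.10 to 0.15 cannot be told from zero.** With 84% power at a true r of 0.15 under random sampling, that is wrong as a general statement.

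**Conclusion.** The point holds as a mismatch between the sample-size rationale and the study it is meant to justify. The 384 is calculated correctly, but for a single proportion in a simple random sample, and the exploratory study has neither. The match to 384.1 and the section's own description of its aims, analysis and sampling are enough to establish this, with p = 0.5 the only value supplied.

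The size depends on further assumptions. Under independent sampling, the half-width for a correlation is about ±0.10 near zero, ±0.09 at 0.3 and ±0.075 at 0.5. The ±0.14 near zero rests on a design effect of 2 that the documents neither give nor rule out. The simple-path figures are proxies; indirect effects and interactions need their own intervals. All of these are sampling-error figures and say nothing about selection bias.

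The sample size itself is not shown to be inadequate. This is a correction the sponsor should make, not a threat to the study's feasibility.

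**What to change.** In the Exploratory Study section:

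1. Keep n = 384 and delete the 5% precision as its rationale.
2. State instead the approximate 95% half-width for a correlation or simple standardised path under independent sampling: ±0.10 near zero, ±0.09 at r = 0.3 and ±0.075 at r = 0.5. Add that it would be about ±0.14 near zero under an assumed, illustrative design effect of 2, and that none of these figures covers selection bias.
3. Reconcile the two descriptions of the sampling method in one statement of how participants are reached.
4. Add a survey item recording the referral source, so that standard errors can allow for referral clustering where the number of chains permits.

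**Cost:** some protocol wording and one survey item. The stated precision becomes less favourable. No extra participants are needed.

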### Phase 2: Program Development

#### Objectives

The aim of Stage 2 is to develop the anticyberbullying intervention program. Past approaches have been ineffective because of a lack of consistency within the community. To achieve this objective, a quasi-experiment with a nonequivalent pretest–post-test control group design will be conducted for a duration of 1-1.5 years (Figure 5).

**Figure 5 figure5:**
[figure not shown]
Overview of the nonequivalent control-group pretest–post-test study.

#### Quasi-experiment with Nonequivalent Pretest–Post-test Control Group Design

The study design for this stage is quasi-experimental, in which the groups are nonrandomized into intervention and control groups and selected purposively. This study will be conducted in public hospitals and private hospitals located in Malaysia. All hospitals are eligible to participate. The selection of hospitals will be randomized for the implementation of the interventions. The randomization of hospitals will be performed by online statistical computing web programming to generate the randomization schedule [22]. The current methodology will help reduce selection bias in the study.

This intervention study will be conducted on TCM practitioners specifically. A baseline assessment will be done, in the intervention and control hospital, to measure the burden of bullying and its correlates using the CBQ and CBQ-S. This stage will begin after the investigation of prevalence and exploratory research. First, baseline information will be collected within 3 months, and then the intervention will be monitored twice after a regular period of 6 months in order to monitor the consistency of the intervention program.

The intervention program will be designed and finalized after (1) a systematic review of systematic reviews of previously published literature on bullying and the effectiveness of antibullying intervention programs; (2) the conducting of focus group discussions with TCM practitioners, patients, and other health care providers (to explore the perceptions, beliefs, and suggestions regarding bullying prevention programs); and (3) the conducting of a consultation workshop with all the stakeholders. The bullying intervention program (BIP) will pretest among 50 participants, which will include health care providers, TCM practitioners, and patients. The multicomponent hospital-based intervention strategy will be administered at 3 levels: (1) patients, (2) TCM practitioners, and (3) other health care providers. All the data of participants in this study will be password-protected and safe using Microsoft OneDrive. The recruitment of participants will follow the same procedure described for the exploratory study and prevalence study.

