**Results:**

The results of this study will determine the pre- and posteffectiveness of an integrated PMMH-I for health care professionals. The prototype system platform will be developed and implemented in a public and private hospital. Results from Phase 1 will be published in 2021, followed by the implementation of Phase 2 in subsequent years.

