#### Data Collection and Analysis

The recruitment of participants will follow the same procedure as was described for the exploratory study and prevalence study. The participant will be invited to join through a webinar to complete the questionnaire. Only the participants who completed Phase 2 will be asked to continue. The prototype will be given to them, and a brief training will be provided through a 30-minute webinar. Stage 3 participants will be limited to the Stage 2 completers in order to gauge the effectiveness of the Step 2 intervention program and whether the prototype is capable of reporting cyberbullying effectively. Thematic analysis will be done on the data yielded from the control and intervention groups. All the data of participants in this study will be password-protected and safe using Microsoft OneDrive.

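### Phase 2 gives two conflicting allocation rules, purposive groups and computer-randomized hospitals, and its selection-bias claim is not supported until one is chosen

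*Protocol article*

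**What the plan says.** The Objectives of Phase 2 in the protocol article state that "a quasi-experiment with a nonequivalent pretest–post-test control group design will be conducted". The section that describes this design opens consistently with that label: "the groups are nonrandomized into intervention and control groups and selected purposively". The caption of Figure 5 also calls the control group nonequivalent, and the Abstract and Study Plan call Phase 2 quasi-experimental.

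The same opening paragraph then describes a random mechanism: "The selection of hospitals will be randomized for the implementation of the interventions". The tool is named too: "The randomization of hospitals will be performed by online statistical computing web programming to generate the randomization schedule". The paragraph closes with a claimed property: "The current methodology will help reduce selection bias in the study".

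The next paragraph ties the arms to hospitals: "A baseline assessment will be done, in the intervention and control hospital". The section ends by carrying over the recruitment procedure of the two Phase 1 studies. The Prevalence Study section describes this as a nonprobability snowball sample, and the Exploratory Study section as convenience and snowball sampling.

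**The concern.** One paragraph gives a purposive rule and a random rule and does not say what each one governs. Two teams could follow it, one choosing the intervention hospitals by judgement and the other drawing them from the schedule, and both could claim compliance.

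Research question 2, on the pre- and post-intervention efficacy of the programme, depends on this comparison. The allocation rule settles whether the comparison is randomized, what the unit of allocation is, and how strong a causal statement the result can carry. If the rule stays open, the study could later be reported as either randomized or quasi-experimental. The sentence about reduced selection bias invites the stronger label.

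**Working it through.** The point rests on no figure in the article. It states no Phase 2 sample size, number of hospitals or intracluster correlation, so there is nothing to reproduce. The check is a comparison of the statements under each reading that could reconcile them.

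**Statements compared**

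- A. Group formation is nonrandomized and purposive (first sentence of the Phase 2 design section; the nonequivalent label agrees).
- B. Hospitals are randomized for implementing the interventions, from a generated schedule (same paragraph).
- C. The method helps to reduce selection bias (last sentence of that paragraph).
- D. Participants are recruited as in Phase 1, by snowball and convenience methods (end of the section, with the Prevalence Study and Exploratory Study sections).

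**Reading 1: the schedule samples hospitals, and arms are then chosen purposively**

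- A and the design label stand.
- B is worded misleadingly, since it ties randomization to implementing the interventions and not only to taking part.
- C can hold in a limited sense: random choice of sites may lessen selection at site level. It gives no protection to the contrast between intervention and control, because arm membership is still a matter of judgement.

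**Reading 2: the schedule assigns hospitals to intervention or control**

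- B stands, and C has support at hospital level.
- The design is then cluster-randomized with the hospital as the unit of allocation. A is wrong, and so are the nonequivalent and quasi-experimental labels.
- It does not help to say that A refers only to choosing participants within hospitals. A describes how groups are placed into intervention and control, which is allocation and not recruitment.

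**Common to both readings**

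Under D, who enters from each hospital is decided by referral and convenience. Selection at participant level therefore remains whichever rule applies to hospitals, and C does not acknowledge it.

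**Result**

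| | Design label (A) | Bias claim (C) for the between-arm comparison |
|---|---|---|
| Reading 1 | stands | not supported |
| Reading 2 | wrong | supported at hospital level only |

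There is no reading under which the label and the bias claim both stand as written.

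**The case against.** The strongest reply is that A and B concern different units: groups in one, hospitals in the other. Random choice of sites combined with purposive grouping is possible, and so is randomization of hospitals with purposive choice of participants. On that view there is no logical impossibility. The bias sentence also claims only to help reduce bias, and Figures 3 and 5, which are not shown here, may make the flow clear.

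Part of this stands. It would be too strong to say that the two statements can never both be true, or that the bias sentence is simply false. The defect is that the article does not say which mechanism assigns arms, and each way of reconciling the sentences leaves another statement wrong or unsupported. A figure might show the intended flow, but it would not remove the conflicting sentences.

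A reader might go further and infer one hospital per arm, with arm fully confounded with hospital or sector. The documents do not support that. The singular in "A baseline assessment will be done, in the intervention and control hospital" is set against plural wording in the same section, where public and private hospitals are named and all are eligible. The Abstract sentence "The prototype system platform will be developed and implemented in a public and private hospital" concerns the prototype, which belongs to Phase 3.

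A reader might also infer that no quantitative comparison is planned, from "Thematic analysis will be done on the data yielded from the control and intervention groups". That sentence is in the Phase 3 section. The Study Plan names quantitative methods and software for each stage, and the Interface Design section names the CBQ and CBQ-S for judging effectiveness. The details of the model may properly sit in a fuller document.

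**Conclusion.** The point holds as a contradictory allocation rule with an unsupported stated property. It is not a complaint about missing detail, because the article states both rules and draws a bias claim from them.

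Its size is categorical: whether the Phase 2 effect is a randomized or a nonrandomized comparison. An inflated false-positive rate from ignoring hospital could be calculated only by assuming an arm size, an intracluster correlation and a naive test. The article states none of these, so no such rate is claimed. Nor does the point require more hospitals or a different design from the one the authors prefer.

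The conclusion assumes only that the sentences quoted are the operative text, and that neither the missing figures nor an unseen full protocol overrides them.

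**What to change.** Choose one rule before any hospital is allocated, and make the design label and the bias sentence match it.

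- **Option (a), randomized.** State that the web-generated schedule already planned assigns hospitals to intervention or control. Delete the nonrandomized and purposive wording and the nonequivalent label, and align the quasi-experimental label in the Abstract and Study Plan. Describe the design as cluster-randomized with the hospital as the unit of allocation, and account for hospital in the CBQ/CBQ-S comparison. Limit the bias sentence to hospital-level allocation, since recruitment of participants remains nonprobability.
- **Option (b), purposive.** Keep the quasi-experimental label. State that any randomization only samples hospitals, or delete the randomization sentences. Remove the selection-bias sentence as applied to the between-arm comparison, and report the effect as a nonrandomized comparison open to confounding by hospital.

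Under either option, state the unit and mechanism of allocation and the number of hospitals.

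The cost is a few sentences of protocol text. Option (a) uses a schedule already planned, and the analysis must then respect the hospital. Option (b) costs strength of conclusion. Once hospitals have been allocated, rewording cannot change how it was done.

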### Research Questions

We aim to explore the following 4 research questions in this study: (1) What is the current workplace cyberbullying status among Traditional Chinese Medicine practitioners (TCM) in Malaysia? (2) What is the pre- and postefficacy of the Personalized Mobile Mental Health Intervention (PMMH-I) on the prevalence of measurable factors (ie, depression, anxiety, and stress) in workforce cyberbullying on TCM practitioners? (3) What are the moderating and mediating factors of workplace cyberbullying on TCM practitioners? (4) What is the technological feasibility of implementing the integrated PMMH-I as a component of routine hospital-based systems?

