### Main Intention and Objective

This study's main intention is to give awareness and authority to the community of health care professionals against cyberbullying by developing a Personalized Mobile Mental Health Intervention program (PMMH-I) in partnership with all health care providers. This partnership will seek to form alliances with public and private institutions to ensure the success and continuation of the program. The PMMH-I program will aim to reduce the psychometric properties of cyberbullying through awareness and adaptation of technology.

The main objective of this protocol is to develop and implement the PMMH-I program to decrease the psychometric properties of cyberbullying in the hospital-based setting in Malaysia. We hypothesize that the creation of PMMH-I programs will come about by executing a PMMH-I strategy that permits the fusion of global and local knowledge. PMMH-I promotes health care community development, thereby increasing social integration between different health care providers such as doctors, nurses, traditional and complementary medical practitioners, pharmacists, and other health care providers.

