### Phase 3: Electronic Anticyberbullying Monitoring System

#### Interface Design

An expert from each stakeholder group (TCM practitioners, other health care professionals, patients, and IT experts) will be involved in the interface design, information system design, and prototype testing. The system’s overall performance and satisfaction will be acquired through questionnaires (questionnaires are available upon request). The CBQ and CBQ-S will be used to determine the effectiveness of an intervention program using a prototype (post-test). The compilation of this research will be used to design the Personalized Mobile Mental Health Intervention (PMMH-I). The duration for stage 3 will be 6 months.

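### Research question 2 asks for an effect on depression, anxiety and stress, but no instrument for any of the three is named in Phases 2 and 3, and no stress instrument is named in any phase

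*Protocol article*

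**What the plan says.** **The efficacy question.** Under Research Questions, the second question asks for the effect of PMMH-I, before and after, "on the prevalence of measurable factors (ie, depression, anxiety, and stress) in workforce cyberbullying on TCM practitioners".

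**Phase 1, Prevalence Study.** Objective 1 is "evaluating the overall prevalence rate of workplace cyberbullying and its related psychological impacts (depression, anxiety, and stress) on TCM practitioner". The scales for psychological impact follow: "The Hamilton Depression Scale (HAM-D) [17], the Hamilton Anxiety Scale (HAM-A) [18], and the clinical anger scale [19] will be used". CBQ and CBQ-S are listed separately, for the prevalence of cyberbullying.

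**Phase 1, Exploratory Study.** Workplace stressors and emotions are constructs in a structural equation model. No instrument is named for any construct.

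**Phase 2, Quasi-experiment.** The baseline in intervention and control hospitals is taken "to measure the burden of bullying and its correlates using the CBQ and CBQ-S". Two later monitoring points are planned, with no instrument named.

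**Phase 3, Interface Design.** "The CBQ and CBQ-S will be used to determine the effectiveness of an intervention program using a prototype (post-test"). The other questionnaires in this phase cover system performance and satisfaction. Data Collection and Analysis adds a thematic analysis.

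**Main Intention and Objective.** The main objective is to develop and implement the program "to decrease the psychometric properties of cyberbullying in the hospital-based setting in Malaysia".

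**The concern.** An effect on depression, anxiety and stress can be estimated only if each is measured before and after the intervention, in both groups. The article is specific about instruments at the Phase 2 baseline and the Phase 3 post-test, and those it names measure cyberbullying. The psychological scales are named only for a survey that precedes the intervention and has no study groups.

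At stake is the only efficacy question in the article. Baseline scores that are not collected before the intervention starts cannot be recovered later, so the omission could not be repaired at analysis.

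Two smaller points go with it. Phase 1 objective 1 promises stress, while the named battery covers depression, anxiety and anger. The main objective does not settle which outcome is meant, because psychometric properties belong to a measuring instrument and are not something that an intervention lowers in participants.

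**Working it through.** No arithmetic on power or sample size applies, and the article gives no figure to reproduce here. The check is to set the outcomes named in research question 2 against the instruments named in each phase.

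| Outcome | Phase 1 prevalence survey (no intervention) | Phase 2 baseline | Phase 2 monitoring, two points | Phase 3 post-test |
|---|---|---|---|---|
| Depression | HAM-D | none named | none named | none named |
| Anxiety | HAM-A | none named | none named | none named |
| Stress | none named (the third scale is for anger) | none named | none named | none named |
| Cyberbullying | CBQ, CBQ-S | CBQ, CBQ-S | none named | CBQ, CBQ-S |

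Counts from the first three rows:

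- Outcomes of research question 2 with a named instrument at any assessment in Phase 2 or 3: 0 of 3.
- Outcomes with a named instrument in Phase 1: 2 of 3 (depression, anxiety).
- Outcomes with no named instrument in any phase: 3 − 2 = 1 (stress).

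Three readings that might close the gap were then checked.

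1. *The Phase 2 baseline also covers correlates of bullying.* The sentence says that these are measured with CBQ and CBQ-S. The Prevalence Study section gives those questionnaires the task of measuring cyberbullying and assigns psychological impact to other scales. The word therefore adds no depression, anxiety or stress measure.
2. *Phase 1 supplies the pretest.* Phase 1 is a snowball survey without intervention and control groups. Phase 2 has its own baseline, in intervention and control hospitals, after Phase 1. Even if Phase 1 scores could be linked to Phase 2 participants, no later HAM-D or HAM-A assessment is named to pair with them.
3. *The exploratory study covers stress.* It includes workplace stressors as a model construct. A stressor is an exposure. Stress in research question 2 is an outcome, and no instrument is named for either.

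**The case against.** The strongest case on the other side is that much of this is inferred from silence. The article names no instrument for the two monitoring points, so it does not say that only cyberbullying questionnaires are used there. Figures 3 and 5, which show the experimental design, are not available in the text and might list more measures. A journal article also condenses a fuller protocol. In addition, the Exploratory Study includes workplace stressors and emotions, and the Discussion promises insight into job, team and organizational stress.

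Part of this stands. A reader might infer that Phases 2 and 3 measure nothing but CBQ and CBQ-S, or that stress is measured in no phase. The text supports neither. Phase 3 also collects performance and satisfaction questionnaires and qualitative data, the monitoring points are left open, and a stress-related construct appears in Phase 1. What the text supports is that no instrument for the three outcomes is *named* in the intervention phases, and no stress instrument is named anywhere.

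The core is not answered. The article did not leave instruments to another document. It names them at the Phase 2 baseline and at the assessment meant to determine effectiveness, and those named do not match the research question. If a figure lists others, text and figure disagree and the text still needs correction.

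A further fair point is that the text leaves unclear which phase tests PMMH-I. Phase 2 describes a bullying intervention program, and Interface Design says that PMMH-I will be designed from the compiled research. Adding scales to Phase 2 alone might therefore not make the question answerable, so the fix has to reach the Phase 3 post-test too.

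The anger scale does no harm in itself. An extra scale prevents no objective from being met. The fault is only that stress is promised and no scale for it is named.

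**Conclusion.** The concern holds as a mismatch within the stated text. None of the three outcomes in research question 2 has a named instrument in Phases 2 and 3 (0 of 3), and one of the three, stress, has none in any phase. Followed as written, the study would yield before-and-after data on cyberbullying but could not answer research question 2, and Phase 1 objective 1 could not be met for stress.

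The parts differ in weight. The mismatch between research question 2 and the instruments of the intervention phases must be resolved before the Phase 2 baseline. The stress and anger mismatch in Phase 1 and the wording of the main objective are smaller and need only a change of text.

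The conclusion assumes that the missing figures list no further measures, and that CBQ and CBQ-S serve in Phases 2 and 3 for what the Prevalence Study section says they measure.

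**What to change.** Choose one of two routes for research question 2.

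- **Keep the question.** Give the Phase 1 depression and anxiety scales, plus one stress scale if stress is kept, in both groups at the Phase 2 baseline, at both monitoring points and at the Phase 3 post-test.
- **Restate the question.** Ask for the effect on CBQ/CBQ-S scores, and make no efficacy claim for depression, anxiety or stress.

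On either route, name the instruments used at the two monitoring points.

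For Phase 1, the Results section says that the prevalence survey began in July 2020. Changing its scales partway would leave early and late respondents with different data, so correct the wording instead: delete stress from objective 1, or state that it is not measured.

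Reword the main objective to name the outcomes that are measured, in place of psychometric properties. The documents do not rank cyberbullying scores against psychological scores. That choice is left to the investigators.

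The first route costs a longer questionnaire at assessments already planned, with no added participants or visits. The second costs wording only, but gives up the mental health claim. The Results section puts the start of Phase 2 recruitment at July 2021, after the Phase 1 work, so on that timeline the change can be made before baseline data are collected.
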